## **6.2 Administration of Behavioral Intervention**

All participants will be instructed to sync their smart powered TB data to the app twice per week. Failure to do so will disqualify the participant from receiving any incentives that week for those in an incentive group. All participants, regardless of group assignment, will receive a fixed payment of \$3 per week for syncing their data every three days (Mondays, Wednesdays, and Fridays specifically). A text message reminder to sync the app will be sent to participants up to every 3 days. For those assigned to the Drawing incentive group, the reminder will also prompt participants to select a drawing number for the coming week. The drawing for performance-based incentives will take place about 72 hours after week's end.

First, all participants will enter a "practice" week at the start of the intervention, during which participants will sync their TB data (and be eligible for the \$3 incentive for syncing), but not be eligible for the performance-based toothbrushing incentive. Following the practice week, participants are eligible to earn incentives over 8 one-week periods for a total of 56 days.

All participants will be notified by text message of their toothbrushing adherence status per the smart powered TB data every week. For participants assigned to a Fixed or Drawing incentive group, the text message will include the amount earned and the total balance accrued thus far during the 2-month pilot trial (i.e., gift cards, virtual drawing tickets and winnings, depending on parental/caregiver reward preferences obtained in the UH2 formative research). Participants will have the option to additionally have the text messages sent to other family members who regularly brush the child's teeth. Contact information for all family members will be obtained at the baseline visit and will initially require that the recipient opt-in: an introductory text message will be sent to the family members asking if they agree to receive the text messages and only those responding in the affirmative will receive text messages during the intervention.

Among children who did not have a documented ChildPlus dental visit at baseline, parents/caregivers in the Fixed incentive group will be eligible for a \$40 reward if they take their child to a dental check-up visit and it is documented in the ChildPlus database by the 2-month follow-up visit. Among children without a ChildPlus documented baseline dental visit in the Drawing incentive group, parents/caregivers whose child has a documented ChildPlus dental visit by the 2-month follow-up will have a 10% chance of winning \$400 in a drawing.

The monetary incentive groups will be told that having a preventive dental visit will earn them an incentive equivalent to 4 weeks of toothbrushing. Thus, the total expected value

of exceeding the higher-adherence threshold throughout the intervention period is \$80 from toothbrushing and \$40 from dental visit attendance.

To claim any incentives, including for syncing data, a parent/caregiver and child must attend the 2-month follow-up visit. All payments will be awarded as gift cards at the 2-month visit, but 2-month follow-up visit questionnaires will determine if another modality would be preferred in the future Phase II/III stage. After returning the TP pump participants will be provided a new TP pump and two new brush heads at the end of the intervention.

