## 6 STUDY INTERVENTION

### 6.1 Description of Behavioral Intervention

Child-parent/caregiver dyads will be assigned in a 1:1:1 ratio to one of three conditions: Control group, a Fixed monetary incentive condition, or a Drawing monetary incentive condition.

In the Control group, participants will not be eligible to receive any performance-based incentives during the first 2 months, but will receive information on their toothbrushing adherence per the smart powered TB data, as well as other informational reminders about oral health care behaviors. After the 2-month follow-up visit, the control group will have the ability to earn Fixed incentives in a delayed (waitlisted) 2-month open label extension. This is not a formal part of the UH2 study evaluation for the future trial preparation, but rather a necessary condition of the trial design to assure that all participating EHS parents/caregivers have the chance to earn the same monetary incentives. They will follow the same procedures (texting notifications) as the Fixed intervention group from the 2-month follow-up to a 4-month follow-up. At the 4-month follow-up visit, they will be able to collect the earned incentives. To receive the rewards the parent/caregiver and child must attend the 4-month visit and return their toothpaste pump. Participants will be provided a new TP pump and 1 new brush head.

In the Fixed monetary incentive group, participants will be eligible to earn one of two incentive amounts every week. They will earn \$5 in incentives if the participant meets a lower adherence threshold (i.e., likely 7 times brushing his/her child's teeth) during the preceding week. They will earn \$10 in rewards if the participant meets a higher adherence threshold (i.e., likely 14 times brushing his/her child's teeth) during the preceding week. The exact thresholds may be modified based on UH2 formative research information being collected prior to the trial.

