### **7.3 2-month Follow-Up Study Visit (Visit 2, T = day 60 ± 28)**

The final study visit for participants randomized to the incentive groups is 2 months after the baseline visit. During this exit visit, a trained staff member will complete the final questionnaire and post-test with the parent/caregiver following the established protocol. The dental provider will perform an oral examination and will provide a referral to a dental home if one has not already been established.

- Administer questionnaire to parent/caregiver.
- Collect the parent/caregiver's child toothbrushing diary and TP pump. Record weight of TP pump.
- Perform dental screening on child participant's teeth (by blinded dental provider); record decay and assess treatment urgency. Children with urgent treatment needs will be referred with a warm handoff to staff at the corresponding dental clinic.
- Apply GUM Red-Cote Liquid plaque disclosing agent to child's teeth (by blinded dental provider) and record plaque score.
- Take extraoral photographs of the facial surfaces of child's anterior teeth.
- Watch the parent/caregiver brush the child's teeth and have the parent brush off the child's plaque disclosing solution.
- Give the parent/caregiver an electronic tablet to watch the Anticipatory Guidance presentation.
- Give the parent/caregiver the accumulated rewards per assigned study group arm. Distribute new TB heads (2 TB heads for the intervention groups; 2 TB heads for control group participants who do not want to continue in the open label Fixed incentives for 2 months; 1 TB head for the control group participants who continue in the open label Fixed incentives program for 2months), TP pump.
- Give the parent/caregiver \$30 compensation for attending the follow-up visit.
- Optional for Control Group only: Explain the intervention procedures and fixed rewards program to the parent/caregiver and have her/him explain it back in her/his own words (teachback).

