### **8.2 Questionnaires**

Research staff will administer CAPI Questionnaires to parents/caregivers during the study visits at baseline and 2-month follow-up, with data entered directly into Qualtrics; questionnaire data will be analyzed for changes in self-reported behaviors and perceptions, including relevant common data elements (CDEs) identified by NIDCR OHDC Collaborative Working Groups. Questionnaire items include demographics, current brushing behaviors, dental visit attendance drawn from BRFQ (Albino et al., in submission), economic module, and POQL (Huntington et al. 2011). Follow-up questionnaires will assess satisfaction/acceptance of the incentives and study procedures, as well as compliance with study procedures, such as whether others in the household used the child's powered toothbrush or toothpaste pump.

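### Recording could differ by arm for both primary behaviours, because payment tied to recorded behaviour exists only in the incentive arms; contrasts with control may be biased toward the incentives

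*Protocol*

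**What the plan says.** **Brushing.** Protocol section 3.2.1 defines primary outcome (a) as the percentage of half-days on which the child's teeth are brushed, and names no instrument. Section 4 bases the weekly brushing payment on smart-toothbrush data, which reach the investigators through the parent's phone app (sections 4 and 8.4.2). Section 6.2 asks everyone to sync twice a week and adds: "Failure to do so will disqualify the participant from receiving any incentives that week for those in an incentive group". In control, section 6.1 says "participants will not be eligible to receive any performance-based incentives during the first 2 months".

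Some support is common to all arms. In section 6.2, "All participants, regardless of group assignment, will receive a fixed payment of" $3 per week for syncing, and "A text message reminder to sync the app will be sent to participants up to every 3 days". All arms also get weekly adherence texts.

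**Dental visits.** Primary outcome (b) is a visit documented in ChildPlus, among children with none there at baseline (sections 3.2.1 and 8.5). Section 6.2 pays Fixed families $40 "if they take their child to a dental check-up visit and it is documented in the ChildPlus database by the 2-month follow-up visit". Drawing families have a 10% chance of $400 on the same condition.

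**Visit 2.** The list in section 7.3 includes "Collect the parent/caregiver's child toothbrushing diary and TP pump. Record weight of TP pump". It mentions no sync of the brush, and families are asked to bring the pump but not the brush (sections 4 and 5.4). Section 8.2 collects parent-reported attendance in all arms: "Questionnaire items include demographics, current brushing behaviors, dental visit attendance drawn from BRFQ". No section compares those reports with ChildPlus.

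**The concern.** A behaviour that has to be recorded before it counts is measured as behaviour multiplied by recording. If recording is equally complete in all arms, this only dilutes the contrast. If one arm has an extra reason to record, part of the contrast is recording and not behaviour.

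Here the extra reason runs one way. A family in an incentive arm that does not sync forfeits a reward that control does not have. A family in an incentive arm whose child saw a dentist has money depending on the ChildPlus entry, and a control family does not. A control visit that took place but was not entered counts as no visit.

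Section 12.3 uses the effect sizes of the two monetary arms against control for the Phase II/III sample size. An inflated effect would make that trial too small.

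**Working it through.** **1. What depends on recording, by arm (sections 6.1 and 6.2).** The protocol's own expected values first:
- Lower tier of the drawing: 0.18 × 25 + 0.01 × 50 = $5.00 (stated $5).
- Upper tier: 0.34 × 25 + 0.04 × 50 = $10.50 (stated $10; the difference does not matter here).
- Dental drawing: 0.10 × 400 = $40, equal to the Fixed reward.
- Eight weeks at the upper tier: 8 × 10 = $80, as stated.

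Money tied to a week's syncing is $3 in control. In Fixed it is 3 + 5 = $8 or 3 + 10 = $13. Over nine weeks, including the practice week, the maximum is 9 × 3 = $27 in control and 27 + 80 = $107 in Fixed, plus $40 for a documented dental visit.

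**2. Dental outcome.** Observed rate = true attendance × share documented. Assume 50% true attendance in both arms and 90% documented in an incentive arm (assumptions, not protocol figures):
- Control 90% documented: 45% against 45%, no difference.
- Control 80% documented: 45% against 40%, 5 points.
- Control 70% documented: 45% against 35%, 10 points.

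With 12 children per arm, and only those without a baseline visit counted, one unrecorded control visit moves the control rate by at least 1/12 = 8.3 points. In a subset of 8 (assumed) it would be 1/8 = 12.5 points.

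**3. Brushing outcome.** This applies only if smart-brush data are the source and unsynced half-days are read as unbrushed. Assume true brushing of 60% of half-days in every arm and 5% never synced in an incentive arm, so 0.60 × 0.95 = 57% is observed there.

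| Control loss (assumed) | Control observed | Difference | Ratio |
|---|---|---|---|
| 5% | 57% | 0 points | 1.00 |
| 10% | 54% | 3 points | 1.06 |
| 20% | 48% | 9 points | 1.19 |
| 30% | 42% | 15 points | 1.36 |

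If the brush keeps its sessions until the next sync, only the stretch after the last sync is lost. Over the 56 incentive days, a 20% loss then means 0.20 × 56 = 11.2 days unsynced at the end, on average per control family. A 5% loss means 2.8 days.

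**4. The 20% selection rule (section 12.3).** A group must be at least 20% better than both other groups. In step 3 Fixed and Drawing both read 57%, so 57/57 = 1.00, and the rule is not met at any level of control loss. Against control alone, a relative 20% would appear once control recording fell to 0.95/1.20 = 79%. Read as 20 points, it would need 0.95 − 0.20/0.60 = 62%. Neither is the stated rule.

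**The case against.** The case on the other side is substantial, and most of it limits the size and reach of the point.

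- *A reader might infer that families must make the ChildPlus entry themselves.* No section says so. Section 16.2 has the data extracted from the Early Head Start (EHS) database, who documents a visit is not stated, and section 5.5.1 blinds EHS home visitors to arm. What remains is the family's own reason to see that the visit gets documented.
- *A reader might infer that every missed sync destroys data.* Section 4 describes syncing as a download from the brush. Nothing says that a late sync loses earlier sessions, so the clear risk is the period after the last sync. Appendix A does mark toothbrushing reports at Visit 2, but neither it nor section 7.3 specifies a sync there.
- *A reader might infer that recording alone could win the selection by the 20% rule.* The rule requires beating both other groups, and Fixed and Drawing share the same sync and ChildPlus conditions. Equal loss in those two arms cannot meet it.
- *Brushing has other measures.* Diary, pump weight and plaque score need no sync and are collected in all arms. Section 12.3 uses them for correlation and concordance, and no text substitutes them for missing brush data.
- *Multiple imputation is planned, and the coding of unsynced half-days may be in the statistical analysis plan.* That is fair for brushing. It does not help the dental outcome, where an unentered visit is not missing: it reads as no visit.
- *Testing these measures is what the pilot is for.* Section 3.2.2 will measure ChildPlus completeness, and section 12.3 will report willingness to sync by group. Both would help to detect a recording difference, but neither corrects the contrast with control.

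**Conclusion.** The point holds as a possible bias, not a demonstrated one. It is firmest for the dental outcome, because that outcome is by definition a documented visit and documentation is paid for in two arms only. For brushing it is conditional on smart-brush data being the source of outcome (a), and on how half-days never synced are coded. The $3 payment, reminders and adherence texts in all arms narrow the sync gap without closing it.

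What is exposed is the contrast of each incentive arm with control, and the effect sizes that section 12.3 passes to Phase II/III. The choice between Fixed and Drawing is much less exposed. The protocol gives no sync or documentation rates, so the figures (5 to 10 points for dental visits, 3 to 15 points for brushing) are illustrations under stated assumptions, not estimates. With equal recording the bias is zero. The change is worth making because it is cheap and can only be made before the visits take place.

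**What to change.** 1. **Brushing.** Ask all families to bring the brush and phone to Visit 2 along with the pump. Add a staff-assisted final sync, before payment, to section 7.3 and Appendix A. Name the source for outcome (a), and treat half-days never covered by a sync as missing, not unbrushed. Confirm with the vendor how long the brush stores sessions, which the protocol does not say.
2. **Dental visits.** Give all three arms the same instruction on getting a visit documented. At Visit 2, compare parent-reported visits (section 8.2) with ChildPlus in every arm. Count a dated visit between baseline and Visit 2 that is confirmed by ChildPlus or, if not entered there, by a record sought in the same way in all arms. The REDCap form in section 16.2 could hold it. Section 3.2.1 places this outcome at three months and section 8.5 at two, so these must be reconciled first.
3. **Reporting.** Report sync completeness and ChildPlus completeness by arm.

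The cost is a line in the visit reminder, a few minutes per family at an existing visit, and reconciliation for at most 36 children. The between-arm effect may come out smaller. Treating unsynced half-days as missing still assumes that brushing on them resembles brushing on synced ones, which is why the final sync matters more than the coding rule. The reconciliation also supports the ChildPlus completeness assessment in section 3.2.2.

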### **6.3 Procedures for Training Interventionists and Monitoring Intervention Fidelity**

The Program Manager will train all research staff members on how to explain intervention procedures and incentive program details to participants. The Program Manager or another supervisor will assess fidelity from 100% of audio recordings during the training period and then from a randomly selected 20% of recordings thereafter every week during the expected 12-week participant accrual. A study-specific checklist of intervention procedures and incentive program details will be used to evaluate fidelity from the recordings. Checklists with less than 90% fidelity during the training period or during baseline visits will be declared inadequate and require re-training staff by the Program Manager. A study co-investigator will train the Program Manager to code fidelity data from the recordings.

### **6.4 Assessment of Subject Compliance with Study Intervention**

Study team presentations to parents/caregivers will involve graphics and teachback to provide information about the randomization process and Fixed monetary incentive and Drawing monetary incentive packages. Presentations will be standardized to ensure consistency. Study team staff will document that the information was presented and that the parent/caregiver explained the procedures back in his/her own words. The parent/caregiver will sign to confirm he/she received the information. Throughout the study intervention, a random selection of 5% of SMS text messages to parents/caregivers will ask for a reply to verify receipt.

---

## **7 STUDY SCHEDULE**

### **7.1 Screening**

Study personnel will contact EHS families to assess eligibility and level of interest in participating in this study.

### **7.2 Enrollment/Baseline**

Based on parent/caregivers' and participating EHS sites' availability, each child will be scheduled for the baseline visit with his/her parent/caregiver. When the family arrives at the EHS site, study personnel will explain in detail the goals and procedures of this pilot study.

#### **Enrollment/Baseline Visit (Visit 1, T = 0)**

- Explain purpose and procedures of study to prospective parent/caregiver participant. Verify inclusion/exclusion criteria.
- Obtain and document consent from subject on study consent form.
- Administer CAPI questionnaire to parent/caregiver.
- Perform dental screening on child participant's teeth (by blinded dental provider); record decay and assess treatment urgency. Children with urgent treatment needs will be referred with a warm handoff to staff at the corresponding dental clinic.
- Apply GUM Red-Cote Liquid plaque disclosing agent to child's teeth (by blinded dental provider) and record plaque score.
- Take extraoral photographs of the facial surfaces of child's anterior teeth.
- Give the family the Oral Hygiene Kit, which includes the smart powered TB and fluoride TP pump. Attach label with child's name.
- Instruct the parent/caregiver on how to sync the TB to his/her smartphone, use the TP pump to show the proper amount of TP, and how to brush the child's teeth. Have the parent brush off the child's plaque disclosing solution.
- Apply 3M Vanish (fluoride varnish) to the child's teeth (by dental provider).
- Give parent/caregiver the opaque envelope with the child's sequence number on the outside (by unblinded study staff); parent/caregiver opens the envelope to reveal the randomized assignment to arm. Explain the intervention procedures and rewards program (if assigned to a reward arm) to the parent/caregiver and have her/him explain it back in her/his own words. Explain control procedures to the parent/caregiver and have her/him explain it back in her/his own words.
- Have the parent/caregiver watch the Anticipatory Guidance presentation on a tablet.

- Schedule the family's next visit (in approximately 3 months) and give the parent/caregiver \$30 compensation for attending the baseline visit.

### **7.3 2-month Follow-Up Study Visit (Visit 2, T = day 60 ± 28)**

The final study visit for participants randomized to the incentive groups is 2 months after the baseline visit. During this exit visit, a trained staff member will complete the final questionnaire and post-test with the parent/caregiver following the established protocol. The dental provider will perform an oral examination and will provide a referral to a dental home if one has not already been established.

- Administer questionnaire to parent/caregiver.
- Collect the parent/caregiver's child toothbrushing diary and TP pump. Record weight of TP pump.
- Perform dental screening on child participant's teeth (by blinded dental provider); record decay and assess treatment urgency. Children with urgent treatment needs will be referred with a warm handoff to staff at the corresponding dental clinic.
- Apply GUM Red-Cote Liquid plaque disclosing agent to child's teeth (by blinded dental provider) and record plaque score.
- Take extraoral photographs of the facial surfaces of child's anterior teeth.
- Watch the parent/caregiver brush the child's teeth and have the parent brush off the child's plaque disclosing solution.
- Give the parent/caregiver an electronic tablet to watch the Anticipatory Guidance presentation.
- Give the parent/caregiver the accumulated rewards per assigned study group arm. Distribute new TB heads (2 TB heads for the intervention groups; 2 TB heads for control group participants who do not want to continue in the open label Fixed incentives for 2 months; 1 TB head for the control group participants who continue in the open label Fixed incentives program for 2months), TP pump.
- Give the parent/caregiver \$30 compensation for attending the follow-up visit.
- Optional for Control Group only: Explain the intervention procedures and fixed rewards program to the parent/caregiver and have her/him explain it back in her/his own words (teachback).

### **7.4 4-month Follow-up Study Visit (Optional for Control Group Only, Visit 3, T = 120 ± 28)**

The final study visit for participants randomized to the delayed control group is 2 months after the 2-month follow-up visit (i.e. 4-months from baseline). The dental provider will perform an oral examination and provide a referral to a dental home if one has not already been established.

- Collect the parent/caregiver's child toothbrushing diary and TP pump.
- Perform dental screening on child participant's teeth (by dental provider); record decay and assess treatment urgency. Children with urgent treatment needs will be referred with a warm handoff to staff at the corresponding dental clinic.
- Give the parent/caregiver an electronic tablet to watch the Anticipatory Guidance presentation.
- Give the parent/caregiver the accumulated fixed rewards. Distribute new brush head and a full TP pump.
- Give the parent/caregiver \$30 compensation for attending the follow-up visit.

